### Randomization

After transfer to NICU wards, eligible infants will be randomly assigned in a 1:1 ratio to receive either NCPAP (experimental group) or NIPPV (active control group) as the initial respiratory support. Treatment allocations will be based on a pre-specified random number table and concealed in sealed opaque envelopes. The treatment allocations sequence will be generated using computer programs (R software) by an independent statistician. Multiple-birth infants will be randomized separately.

### Quality control

This trial follows the Good Clinical Practice (GCP) standards. This trail also meets the requirements of the Ethics Committees and is carried out under the supervision of the Ethics Committees of the participating institutions. A Data Safety Monitoring Board (DSMC) will be established, consisting of two independent neonatologists and an independent statistician. DSMC review points will be set up for trial progress and safety.

### Blinding

Operators, clinicians and nurses will not be blinded to the intervention allocation, but independent outcome evaluators and data analysts will be blinded to the allocation. To reduce bias, predefined objective criteria will be specified for the main outcomes of treatment failure in order to provide clear guidance to outcome evaluators.

### Assessment points

The assessments will be performed at predetermined points after randomization (Table 1). The primary end point is at 72 h after birth. Changes in Silverman Anderson Score, oxygen saturation, blood gas, respiratory support mode, ventilator parameters and/or outcomes will be monitored and documented at allocation, at pre-surfactant administration, and at 12 h, 24 h, 48 h, 72 h, 7 days after allocation, at a post-menstrual age of 36 weeks, and at discharge.

**Table 1 T1:** List of measures and assessment points.

**Measure**	**Assessment point**								
	**Allocation**	**Post-allocation**							
	**Within 0.5 h** **after birth**	**Pre-surfactant** **administra-tion**	**12 h**	**24 h**	**48 h**	**72 h**	**Day 7**	**PMA 36**	**Discharge**
Clinical index									
Silverman Anderson score	×	×	×	×	×	×	×		
Oxygen saturation	×	×	×	×	×	×	×	×	×
Blood gas		×		×	×	×			
Respiratory support mode	×	×	×	×	×	×	×	×	×
Ventilator parameters	×	×	×	×	×	×	×	×	×
Outcomes assessment									
NIV treatment failure						×	×		
intubation (%)			×	×	×	×	×	×	×
Pneumothorax (%)			×	×	×	×	×	×	×
Nasal trauma (%)			×	×	×	×	×	×	×
Pulmonary hemorrhage (%)			×	×	×	×	×	×	×
hsPDA (%)			×	×	×	×	×	×	×
IVH grade III or IV (%)			×	×	×	×	×	×	×
White matter injury (%)			×	×	×	×	×	×	×
Blood culture-confirmed sepsis (%)			×	×	×	×	×	×	×
BPD (%)								×	
NEC stage I or II (%)			×	×	×	×	×	×	×
ROP (%)								×	×
NCPAP or NIPPV (hours)									×
IMV (hours)									×
Supplemental oxygen (days)									×
Costs associated with hospital care									×

*NIV, non-invasive ventilation; hsPDA, hemodynamically significant patent ductus arteriosus; IVH, intraventricular hemorrhages; BPD, bronchopulmonary dysplasia; NEC, necrotizing enterocolitis; ROP, retinopathy of prematurity; NCPAP, nasal continuous positive airway pressure; NIPPV, non-invasive positive pressure ventilation; IMV, invasive mechanical ventilation*.

### Planned intervention

Preterm infants with spontaneous breaths will be stabilized on non-invasive respiratory support (PEEP of 6 cmH_2_O and FiO_2_ ≤ 0.40) in the delivery room and during admission to NICUs, and then randomly selected to start NCPAP or NIPPV within 30 min of birth.

#### NCPAP group

The ventilators parameter of the NCPAP group will be set with a PEEP of 6 cmH_2_O (adjustment range 6–8 cmH_2_O) and an FiO_2_ of 0.21–0.40, in order to maintain an oxygen saturation level of 90–95%.

#### NIPPV group

NIPPV will be set in a synchronized mode with a PEEP of 6 cmH_2_O (adjustment range 6–8 cmH_2_O), peak inspiratory pressure (PIP) of 15 cmH_2_O (regulation range 15–20 cmH_2_O), inspiratory time of 0.3 s (regulation range 0.3–0.4 s), respiratory rate of 30 times/min (regulation range 20–40 times/min) and FiO_2_ of 0.21–0.40.

#### MISA method

Under NCPAP or NIPPV, the calf pulmonary surfactant (Calf pulmonary surfactant, Beijing Double-crane pharmaceutical Co. LTD) will be administered *via* MISA method within 120 min after birth if infants are clinically diagnosed with RDS. While the infants are on ventilator support by NCPAP or NIPPV, a direct laryngoscope and a specifically designed thin catheter with 1.67 mm in diameter (LISA catheter^®^, Beijing Double-crane pharmaceutical Co. LTD) will be used to finish the surfactant administration. A direct laryngoscope will be introduced to provide a glottal view before the operator inserts the LISA catheter^®^ 0.5–1.0 cm below the inverted V-shaped vocal cords. After withdrawing the laryngoscope, the operator will fix the thin catheter at the infant's mouth corner with the forefinger and thumb, and the end of the LISA catheter^®^ will be connected to a 5 ml syringe containing surfactant solution. The surfactant will be administered through the LISA catheter^®^ by a nurse within 120–300 s by mini-boluses. The LISA catheter^®^ will be immediately removed after surfactant administration. If an infant develops bradycardia or desaturation (SPO_2_ <85%), stop surfactant administration, keep the LISA catheter^®^ in place, gently touch the infant's back to stimulate spontaneous breaths, increase FiO_2_ and wait for the heart rate and SPO_2_ to return to normal range before finishing the remaining surfactant with cautions. If the heart rate and SPO_2_ continue to drop with the occurrence of apnea, the NIPPV or NCPAP ventilator should be used for positive pressure ventilation immediately, and the operation will be continued after heart rate and SPO_2_ return to normal. If surfactant regurgitation occurs, suspend administration and slow down the infusion until there is no regurgitation in the mouth.

#### Therapy

The first dose of pulmonary surfactant is 100 mg/kg, and the criteria of repeated use of surfactant are as follows: (1) within 72 h after birth; (2) progressively aggravated respiratory distress after first dose with a minimum interval of 4–6 h; (3) chest X-ray is consistent with the imaging findings of RDS; (4) dyspnea caused by other causes is excepted.

The decision for intubation and IMV within 72 h and 7 days after birth of life is based on the following criteria: (1) severe respiratory acidosis with PaCO_2_ > 65 mmHg and pH <7.2; (2) hypoxemia with SpO_2_ of <0.85 on FiO_2_ > 0.4; (3) recurrent apnea with ≥3 episodes per hour or a single episode of apnea requiring positive pressure ventilation within 24 h; (4) SAS increasing > 2 points per hour, or SAS > 5 points lasting more than 2 h after first or second dose of surfactant administration; (5) pulmonary hemorrhage; (6) cardiopulmonary arrest requiring intubation; (7) neonatologists in the NICU believe that invasive respiratory support should be given to patient. Extubation criteria are established as mean airway pressure (MAP) <8 cm H_2_O and FiO_2_ <0.3.

The decision for weaning of NCPAP or NIPPV is based on the following criteria: (1) the infant has recovered from RDS; (2) the signs of respiratory distress have disappeared and SAS <3 points; (3) when NCPAP with PEEP <3–5 cmH_2_O, or when NIPPV with MAP <6–7 cmH_2_O and FiO_2_ ≤ 25%; (4) without apnea or intermittent hypoxia.

After being assessed by the NICU clinicians to meet all the conditions and lasting for more than 24 h, withdrawal of NIV can be considered.

All of the enrolled infants will be started on caffeine soon after admission at a loading dose of 20 mg/kg followed by a maintenance dose of 5–10 mg/kg.

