### Outcome measures

#### Primary outcome measure

The primary outcome is NIV treatment failure within 72 h after birth, as determined by objective oxygenation, blood gas, and apnea criteria, or the need for intubation and mechanical ventilation.

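### Intubation on clinician belief alone counts as primary failure in an open-label trial whose stated protection against bias is objective failure criteria

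*Protocol article*

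**What the plan says.** Three sections of the protocol article bear on this.

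- **Blinding.** Treating staff know the arm: "Operators, clinicians and nurses will not be blinded to the intervention allocation". Two safeguards are offered. First, "independent outcome evaluators and data analysts will be blinded to the allocation". Second, to reduce bias, "predefined objective criteria will be specified for the main outcomes of treatment failure".
- **Primary outcome measure.** Failure within 72 h of birth is defined in two limbs: "as determined by objective oxygenation, blood gas, and apnea criteria, or the need for intubation and mechanical ventilation". Either limb is enough.
- **Therapy.** The list of intubation criteria opens with "The decision for intubation and IMV within 72 h and 7 days after birth of life is based on the following criteria". Criteria (1) to (6) cover respiratory acidosis, hypoxemia, apnea, the Silverman Anderson Score, pulmonary hemorrhage and cardiopulmonary arrest. The last is "7) neonatologists in the NICU believe that invasive respiratory support should be given to patient", with no threshold attached.

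The article does not say that an intubation under (7) must also meet another criterion, or that it is recorded, adjudicated or analyzed separately.

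**The concern.** In an open-label trial, an outcome that depends on a treatment decision can follow the decision-maker's view of the two modes. The article recognizes this risk and answers it with objective criteria. Criterion (7) lets events reach the primary outcome without passing any such criterion. Blinding the evaluators does not close the gap, because the clinician's decision is itself the event.

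At stake is the non-inferiority conclusion. If clinicians intubate more readily on NCPAP, failures are added to that arm and a true non-inferiority may be missed. If they intubate more readily on NIPPV, failures are added to the comparator and an inferior NCPAP may pass the margin.

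**Working it through.** **Tracing the event.** An infant on NIV meets none of criteria (1) to (6). At 40 h, say, the neonatologist judges that invasive support is needed and intubates under (7). The first limb of the primary outcome is not met; the second is. The infant is a primary failure, and a blinded evaluator reading the chart can only agree that intubation took place.

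**Inputs (Sample size calculation).** Failure 24.5% on NCPAP and 22.4% on NIPPV; margin 10 points; upper limit of a two-sided 95% CI (one-sided 0.025); power 80%; 452 per arm; 6% increase to 480 per arm.

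**Reproducing the plan's figure.** With unpooled variance,

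n = (1.960 + 0.842)² × [0.245 × 0.755 + 0.224 × 0.776] / (0.10 − 0.021)² = 7.849 × 0.3588 / 0.006241 ≈ 451.2, so 452 per arm.

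452 × 1.06 = 479.1, so 480. The stated sample size is correct.

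**Sensitivity to arm-dependent discretion.** The chance of declaring non-inferiority is

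Φ[(0.10 − d)/SE − 1.96], with SE = √{[p₁(1 − p₁) + p₂(1 − p₂)]/n},

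where p₁ is the NCPAP rate, p₂ the NIPPV rate and d = p₁ − p₂.

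The documents do not give the share of intubations made only under (7), so a net excess of 0 to 5 points in one arm is assumed. One point is 0.01 × 452 ≈ 4.5 infants; two points are about 9.

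Worked case A, 2 points added to NCPAP at the planned rates: p₁ = 0.265, p₂ = 0.224, d = 0.041, SE = 0.0286; 0.059/0.0286 − 1.96 = 0.106; Φ = 54.2%.

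Worked case B, 2 points added to NIPPV when NCPAP is truly worse by exactly the margin (32.4% against 22.4%): p₂ = 0.244, d = 0.080, SE = 0.0299; 0.020/0.0299 − 1.96 = −1.29; Φ = 9.8%.

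| Assumed excess (points) | A: on NCPAP, power at planned rates | B: on NIPPV, false non-inferiority at the margin |
|---|---|---|
| 0 | 80.1% | 2.5% |
| 1 | 68.2% | 5.2% |
| 2 | 54.2% | 9.8% |
| 3 | 39.9% | 16.8% |
| 5 | 16.8% | 37.6% |

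With the full 480 per arm the pattern is the same: 2 points give 56.7% (A, from 82.4%) and 10.2% (B).

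**Equal discretion is not the problem.** Adding 2 points to both arms leaves power at 77.9%, and 5 points to both leaves 75.0%. The difference between arms does the damage.

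**The case against.** Five arguments deserve weight.

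1. *The link is inferred.* The criteria stand under Therapy and the primary outcome section does not cite them. Table 1 lists NIV treatment failure and intubation as separate rows, and the full protocol may define failure more tightly. This limits certainty. Still, both sections concern intubation in the same 72 h, and on the printed text the second limb takes in a criterion (7) intubation.
2. *The two limbs are stated openly.* True: the primary outcome section does not claim to be wholly objective. The conflict lies with the Blinding section, which presents objective criteria as the bias control.
3. *Withholding intubation on NCPAP cannot do much.* A reader might infer that clinicians who favor NCPAP could manufacture non-inferiority by delaying intubation. The first limb largely blocks this: an infant who reaches an oxygenation, blood gas or apnea criterion has failed whether or not a tube is placed. Removing 3 points from 32.4% would need at least 3/32.4 = 9% of NCPAP failures to meet none of those criteria, and 5 points would need 15%. The documents give no such share. The more credible route to a false claim is extra criterion (7) intubation on NIPPV, shown in column B.
4. *Every shift is assumed.* This stands. The Conclusion's remark that non-inferiority is expected restates the hypothesis and is not evidence of lenient intubation.
5. *Taking (7) out of the primary outcome would be worse.* This also stands. It would score infants whose NIV had ended as successes, and early intubation can prevent an objective criterion from ever being reached.

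**Conclusion.** The point holds as an inconsistency between the Blinding, Primary outcome measure and Therapy sections that leaves the primary outcome open to arm-dependent judgment. Bias is possible, not shown, and it could run either way. Only 7.9 points separate the assumed difference (2.1) from the margin (10), so a net excess of about 9 infants in one arm of 452 matters. It takes power from 80% to 54%, or the false-claim rate at the margin from 2.5% to about 10%, depending on the arm. These figures rest on the planning rates, a normal approximation, and assumed shifts made up of infants who would not otherwise have failed.

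The documents do not support saying that the trial is biased toward NCPAP, that the clinician-judgment clause should go, or that the sample size is wrong.

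**What to change.** Leave the freedom to intubate and the primary outcome unchanged, with every intubation within 72 h counted as failure. Then:

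1. Reconcile the three sections. State that the second limb includes intubations under (7), and that the objective criteria named under Blinding do not cover them.
2. Record on the CRF which criterion triggered each intubation.
3. Have the blinded evaluators already planned check, from recorded data, whether an objective criterion was met. Fix in advance which criteria count as objective: the primary outcome section names only oxygenation, blood gas and apnea, and criterion (4) rests partly on a bedside score.
4. Report intubations made only under (7) by arm.
5. Prespecify a sensitivity analysis of failure by the objective criteria alone, against the same 10% margin, and qualify any non-inferiority claim if it disagrees with the primary analysis.

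The cost is one CRF field, some wording, a chart check by evaluators already in place, and one analysis. The trigger should be captured prospectively, since it is hard to reconstruct later. The sensitivity result needs care in reading: an infant intubated early under (7) may never reach an objective criterion, so that analysis can undercount failures in whichever arm has more such intubations.

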### Outcome measures

#### Primary outcome measure

The primary outcome is NIV treatment failure within 72 h after birth, as determined by objective oxygenation, blood gas, and apnea criteria, or the need for intubation and mechanical ventilation.

#### Secondary outcome measures

The secondary outcomes are as follows:

NIV treatment failure within 7 days after birthRate of intubationRate of pneumothoraxRate of nasal traumaRate of pulmonary hemorrhageRate of hemodynamically significant patent ductus arteriosus (hsPDA)Rate of intraventricular hemorrhages (IVH, grade III or IV)Rate of white matter injuryRate of blood culture-confirmed sepsisRate of bronchopulmonary dysplasia (BPD)Rate of necrotizing enterocolitis (NEC, ≥stage II)Rate of retinopathy of prematurity (ROP)Duration of NCPAP/NIPPV, duration of IMV, and days on supplemental oxygenCosts associated with hospital care and treatment.

#### Data collection and diagnoses

Patient demographic data mainly include: gestational age, birth weight, sex, multiple births, antenatal corticosteroids use, mode of delivery, maternal complications, Apgar score and cord blood gas. Clinical data mainly include: SAS, requiring more than one dose of surfactant, blood gas, the need for IMV within 72 h and 7 days after birth, duration of NCPAP/NIPPV, days on IMV, days on supplemental oxygen, costs associated with hospital care, morbidity of BPD, pneumothorax, nasal trauma, pulmonary hemorrhage, hsPDA, IVH, white matter injury, blood culture-confirmed sepsis, NEC and ROP.

The clinical diagnosis of RDS will be based on clinical manifestations (respiratory rate > 60/min, nasal flaring, retractions, grunting, or skin cyanosis) and (FiO_2_) > 0.3 for (SpO_2_) > 85%, or SAS > 5 points or SAS increasing > 2 points per hour (17). BPD will be diagnosed according to the National Institutes of Health criteria (18). Pneumothorax will be diagnosed by the presence of air in the pleural cavity in a chest X-ray. Pulmonary hemorrhage will be diagnosed based on the gushing of bloody fluid from the upper airway or endotracheal intubation and when the chest X-ray is consistent with the relevant clinical findings. The diagnosis for hsPDA will be based on clinical signs and echocardiogram (19). IVH and white matter injury will be diagnosed by cranial ultrasound examination, and IVH will be graded by the Papile classification system (20). Blood culture-confirmed sepsis will be defined as clinical sepsis with evidence of pathogens in blood culture. NEC will be graded according to the modified Bell's classification system (21). The diagnosis and staging of ROP will be based on retinal examination by a consultant ophthalmologist.

### Safety procedures

All eligible infants will be monitored by researchers throughout the study to ensure their safety. Any serious adverse events or important adverse events will be assessed by the neonatologists in each center and by the principal investigator. This study adheres to the principle of subject protection and discontinues the experiment in time if any adverse events occur, regardless of whether they are related to this study or not.

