At present, NCPAP and nasal intermittent positive pressure ventilation (NIPPV) are the two most common non-invasive ventilation (NIV) modes for the initial respiratory support in NICUs (7). NIPPV imposes no more than 30 times per minute ventilator inflations to a set peak pressure (maximum 15 cmH_2_O) and may be delivered by short binasal prongs to very preterm infants. NIPPV has been used in NICUs for a variety of indications, especially for extubation ventilation support. It could reduce intubation due to frequent primary apnea, asynchronous thoracoabdominal motion, and inspiratory effort, and improve the stabilization of the chest wall and the tidal and minute volumes (8, 9). However, compared with NCPAP, NIPPV might be more invasive and might involve more risks to very preterm infants. An association has been found between the use of NIPPV and the increased risk of abdominal distention, vomiting and gastrointestinal perforation (10, 11). In view of the gentle ventilation support strategy to the tiny, very preterm infants during the birth transition period, there is lack of high-quality evidence to support the superiority of NIPPV to NCPAP.

RDS remains a significant problem for preterm infants, although its management has evolved in the “post-surfactant era”, resulting in improved survival of the very preterm infants (12). The optimal approach to administering pulmonary surfactant (PS) has attracted great attention in neonatology in recent years. The transition from intubation-surfactant-extubation (InSurE) to less-invasive surfactant administration (LISA) and minimally-invasive surfactant therapy (MIST), and the minimal invasive surfactant administration (MISA) with specially designed minimally invasive tubes in China, as well as administration of PS with laryngeal masks and aerosol inhalation, reflects the efforts to minimize lung trauma and the application of gentle ventilation strategy, as much as possible, in the care of very preterm infants in NICU (13, 14).

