### Sample size calculation

The failure rate of NCPAP with MISA approach was 24.5% (of NIPPV, 22.4%) in preterm infants aged <32 weeks with RDS (15). There was no statistical difference between the two groups. We have set the non-inferiority margin for the trial at 10%. That is, NCPAP is supposed to be non-inferior to NIPPV if the difference in risk of NCPAP treatment failure and the upper limit of its bilateral 95%CI is <10%. To demonstrate this with 80% power, 452 infants per study group are required. In order to prevent the loss of samples, the sample size is increased by 6%. Therefore, a total of 960 samples will be selected and allocated randomly 1:1 into the two study groups (480 in the NCPAP group and 480 in the NIPPV group).

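### The safety paragraph stops the experiment for any adverse event, related or not, which as written conflicts with recording adverse outcomes to discharge and with intention-to-treat

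*Protocol article*

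**What the plan says.** The Safety procedures section of the protocol article has two operative sentences. The first concerns assessment and carries a severity limit: "Any serious adverse events or important adverse events will be assessed by the neonatologists in each center", and also by the principal investigator. The second concerns stopping and carries none: the study "discontinues the experiment in time if any adverse events occur, regardless of whether they are related to this study or not". It does not say whether the experiment means the allocated respiratory mode, the infant's participation or the whole trial.

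Four other parts of the article bear on this.

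- **Outcomes and follow-up.** Data collection and diagnoses lists "morbidity of BPD, pneumothorax, nasal trauma, pulmonary hemorrhage, hsPDA, IVH, white matter injury, blood culture-confirmed sepsis, NEC and ROP" among the clinical data. Table 1 schedules pneumothorax, nasal trauma, pulmonary hemorrhage, sepsis and NEC at every point from 12 h to discharge. The text above it includes assessments at "7 days after allocation, at a post-menstrual age of 36 weeks, and at discharge".
- **Analysis.** Outcome data specifies analysis by original allocation under intention-to-treat.
- **Clinical decisions.** Therapy gives seven criteria for intubation, introduced by "The decision for intubation and IMV within 72 h and 7 days after birth of life is based on the following criteria", and separate criteria for weaning. None refers to adverse events as such.
- **Trial-level safety.** Quality control provides for a data safety monitoring board with review points for progress and safety.

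**The concern.** Many of the events that would trigger the stopping sentence are also outcomes the trial intends to count. A stopping rule that fires on them works against measuring them, and the consequence depends on what is stopped.

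If participation ends, an infant whose event occurs before 72 h and is not itself a treatment failure has no primary outcome. That loss is related to the infant's condition and possibly to the arm. Later secondary outcomes are lost as well, and intention-to-treat cannot be carried out on data that were not collected.

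If only the mode stops, outcomes can still be counted. Unblinded staff would nevertheless have to abandon the allocated mode for minor or unrelated events. In a non-inferiority trial such departures pull the arms together. They need not be balanced, because the Background reports that "An association has been found between the use of NIPPV and the increased risk of abdominal distention, vomiting and gastrointestinal perforation". If NIPPV is truly better, stops concentrated in that arm move the result toward non-inferiority.

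**Working it through.** **1. The texts side by side.** Nasal trauma is a secondary outcome assessed from 12 h onward. It is not among the named intubation criteria (1) to (6) in Therapy, so it can trigger the stopping sentence without being a treatment failure. Abdominal distention and vomiting are neither among those criteria nor listed outcomes, yet the sentence covers them. Recording nasal trauma to discharge and ending an infant's participation at its first occurrence cannot both be done.

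**2. The plan's sample size reproduces.** Inputs from Sample size calculation: failure 24.5% (NCPAP) and 22.4% (NIPPV), margin 10 points, two-sided 95% CI, power 80%.

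- Variance sum: 0.245×0.755 + 0.224×0.776 = 0.3588.
- n = (1.96 + 0.8416)² × 0.3588 / (0.10 − 0.021)² = 451.2, so 452 per arm, as stated.
- 452 × 1.06 = 479.1, so 480 per arm, as stated ("In order to prevent the loss of samples, the sample size is increased by 6" per cent).
- Allowance: 480 − 452 = 28 per arm, or 28/480 = 5.8% of those enrolled.

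With SE(n) = √(0.3588/n), power is Φ((0.10 − 0.021)/SE − 1.96). If loss were non-informative, this gives 82.4% at n = 480, 80.1% at 452, 78.3% at 432 and 73.4% at 384.

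**3. If participation ends (assumed exits).** Let L infants per arm leave before 72 h, with n = 480 − L observed at the planning rates. The observed upper limit is 2.1 + 1.96 × SE(n) in points. Let failure among removed infants be b on NIPPV and b + d on NCPAP. The full-data rates are then (n×0.245 + L(b+d))/480 and (n×0.224 + L×b)/480. Solving for the d at which the full-data upper limit equals 10 points:

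| L per arm | Observed upper limit (points) | d needed, b = 22.4% | d needed, b from 0 to 40% |
|---|---|---|---|
| 28 (plan's allowance) | 7.6 | 44 points | 43–46 |
| 48 (assumed) | 7.7 | 27 points | 25–28 |
| 96 (assumed) | 8.1 | 14 points | 13–16 |

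**4. If only the mode stops (assumed switching).** All 480 per arm are followed and the true difference sits at the margin (32.4% vs 22.4%). A share c of an arm takes the other arm's risk. The chance of a false non-inferiority claim is Φ((0.10 − D)/SE − 1.96), where D is the diluted difference. With c = 0 it is 2.5%.

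| c | NIPPV arm only: D, false claim | Both arms: D, false claim |
|---|---|---|
| 5% | 9.5 points, 3.7% | 9.0 points, 5.4% |
| 10% | 9.0 points, 5.3% | 8.0 points, 10.3% |

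Every L except 28, every b and c, and the margin-level true difference are assumptions. The documents give none of them.

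**The case against.** The strongest reply is that the literal reading is not the intended one. The sentence follows one about serious or important events, and its adverse events may refer back to those. Table 1 schedules these same events to discharge, and the analysis is by allocation. A plan that counts NEC to discharge can hardly mean that the first complication ends data collection. The operational meaning of discontinuation may also sit in the full protocol, which is not shown.

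Much of this stands. A reader might infer that the trial intends to drop infants at their first adverse event. Table 1 and the intention-to-treat statement point the other way, so the documents do not support that inference. The missing definition alone could be left to a fuller document. What does not fall away is the rule the article states: it names any event, adds unrelated ones, and puts the severity words only in the sentence on assessment. Fourteen centres with unblinded staff could apply it differently.

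A reader might also see a flat contradiction with the MISA method section, under which after bradycardia, desaturation or apnea "the operation will be continued after heart rate and SPO_2_ return to normal". That follows only if such transient events count as adverse events, and nothing says they do.

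Finally, criterion (7) in Therapy already lets unblinded neonatologists intubate at their discretion, so not every departure from the mode could be attributed to this sentence. This too is fair.

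**Conclusion.** The point holds as a badly fixed rule. As written, the sentence conflicts with recording adverse outcomes to discharge and with intention-to-treat, and it should be replaced.

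It would be too strong to say that the trial's conclusion is biased or that power is materially lost. The documents contain no event, exit or switching rates, so the effect cannot be sized. At the plan's own allowance of 28 exits per arm the result is fairly robust, needing a 44-point excess of failure among removed NCPAP infants to reach the margin. It becomes fragile only if exits are common, for example 14 points at an assumed 96 per arm. The dilution figures, from 3.7% to 10.3% against a nominal 2.5%, require a true difference at the margin and switched infants taking the other arm's full risk. The article does not say what support replaces a stopped mode.

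**What to change.** Replace the stopping sentence with three separate statements.

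1. **Stopping the mode.** The allocated mode may be stopped when the treating neonatologist judges that a serious adverse event, or an adverse event plausibly related to the mode, makes continuing unsafe, or on the Therapy criteria. It is not stopped automatically for any event or for unrelated ones. This keeps bedside judgement for non-serious but mode-related problems such as distention or nasal trauma.
2. **Continuing follow-up.** Stopping the mode does not end participation. Every randomised infant is followed through the 72 h, 7-day, 36-week and discharge assessments and analysed as allocated, unless parents withdraw consent for data.
3. **Stopping the trial.** This decision rests with the safety board review already planned under Quality control.

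The cost is wording and slightly more tracking of infants whose mode was stopped. No infants or procedures are added, since Table 1 already schedules the assessments.
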